### 2.12. Descriptive Statistical Methods

Initially, descriptive statistics will be used to summarize the demographic characteristics and dependent variables of the study participants. The following statistical methods will be applied:Means and Standard Deviations: These measures will summarize the central tendency and variability of metric demographic and dependent variables, providing insights into their average values and dispersion [22].Frequencies and Percentages: These methods will describe the distribution of categorical data, such as the participants’ class standings and employment status, outlining the composition of the sample [22].Chi-Square Test: This test will be used to examine differences in categorical variables across independent variables. It will be applied at the pre-test to compare demographic categorical variables between the experimental and comparison groups [22].Independent Sample t-test: This test will compare the means of continuous variables across independent variables. It will be employed at the pre-test to evaluate differences in MTM constructs and other continuous variables between the experimental and comparison groups [22].

### 2.13. Inferential Statistical Methods

This study utilizes the following inferential statistical methods to evaluate the intervention’s impact as indicated in Table 3:Two-Way Mixed Analysis of Variance (ANOVA): The repeated measures analysis will be used to assess mean differences over time (pre-test, post-test, follow-up) within subjects and between the experimental and comparison groups. This test will be applied to evaluate changes in PGSI scores and MTM construct scores across the three-time points, capturing both within-subject effects (e.g., changes over time) and between-group effects (e.g., differences between the experimental and comparison groups due to the intervention) [23]. This approach allows for a thorough understanding of how the participants’ gambling behaviors and MTM constructs evolve during the course of the intervention, while accounting for the repeated nature of the measurements.Mixed Analysis of Covariance (ANCOVA): If significant baseline differences are identified in key variables (e.g., PGSI scores, MTM construct scores, or demographic factors like age or gender), an ANCOVA will be incorporated into the model to control for these differences. For instance, if the participants in one group have significantly higher baseline PGSI scores, the ANCOVA will adjust for this disparity, ensuring that the observed effects on responsible gambling behavior are attributable to the intervention rather than to pre-existing variations between groups [23]. This statistical approach enhances the precision of the findings by accounting for baseline differences, allowing for a more accurate assessment of the intervention’s impact.

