### 2.3. Sample Size Calculation

A power analysis was conducted using G*Power (version 3.1) [18] to estimate the required sample size for this study. Based on a Two-Way Mixed Analysis of Variance (ANOVA) with a medium effect size of 0.30, two intervention groups, three time points (pre-, post-, and follow-up), an alpha level of 0.05, and a beta of 0.20 (80% power), the analysis assumed a correlation of 0.5 among repeated measures and applied a non-sphericity correction of 1. The calculation indicated a required sample size of 20 participants per group. To account for potential attrition and missing data, the sample size was increased by 50%, resulting in a total of 60 participants, with 30 in each group.

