### 2.4. Study Procedure

Participant recruitment will target college students aged 21 and older at the university. The recruitment efforts will include email invitations that introduce this study and invite eligible students to participate. The intervention sessions will be conducted in person. The participants will be randomly assigned to either the experimental group (RESPONSIBLEPLAY^©^: MTM-based intervention) or the comparison group (knowledge-based intervention) using SAS PROC SURVEYSELECT. Participant data will first be imported from an Excel file, and each participant will be assigned a unique ID. Simple random sampling (SRS) will then be conducted using PROC SURVEYSELECT, ensuring equal probability of assignment to either group. A fixed seed (12345) will be used to ensure reproducibility. The function will generate a selection indicator (Selected = 1 for the experimental group and Selected = 0 for the comparison group), which will be used to assign the participants accordingly. The final randomized dataset, including group assignments, will then be exported for implementation.

The intervention will be conducted over three weeks, with one session scheduled per week. Each session will span three days, offering multiple time slots to accommodate the participants’ schedules. This approach ensures that all the participants receive the same intervention content while allowing flexibility in attendance. The first session (Week 1) will include an orientation, completion of the pre-intervention survey, and the start of the intervention activities. The final session (Week 3) will consist of intervention activities followed by the post-intervention survey.

To enhance attendance and engagement, the participants will receive email reminders before each session. Additional reminders will be sent to the experimental group between sessions and after the intervention to reinforce the practice of responsible gambling behaviors. At the eight-week follow-up, the participants will attend a final assessment session, which will be scheduled in advance. Email reminders will also be sent to maximize participation.

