Descriptive statistics (means, SDs)	Summarize continuous variables such as age and baseline MTM/PGSI scores.
Descriptive statistics (frequencies, %)	Describe categorical variables such as gender, class standing, and gambling types.
Chi-Square Test	Assess baseline equivalence in categorical variables between intervention and comparison groups.
Independent samples t-test	Assess baseline equivalence in continuous variables (e.g., PGSI, MTM scores) across groups.
Two-Way Mixed ANOVA	Evaluate within- and between-group differences in PGSI and MTM constructs over time (pre-, post-, follow-up), to assess efficacy of the MTM-based intervention.
Mixed ANCOVA (if needed)	Adjust for baseline differences in key variables (e.g., age, PGSI) when detected.

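### Section 2.13 and Table 3 attach the intervention effect to the between-group effect of a three-wave ANOVA that includes the pre-test, and never name group-by-time as the efficacy test

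*Protocol article*

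**What the plan says.** Section 2.13 plans a two-way mixed ANOVA of PGSI and MTM construct scores to "assess mean differences over time (pre-test, post-test, follow-up) within subjects and between the experimental and comparison groups". It describes the model as "capturing both within-subject effects (e.g., changes over time) and between-group effects", and illustrates the second of these as "between-group effects (e.g., differences between the experimental and comparison groups due to the intervention". Table 3 gives the purpose of the same model as "Evaluate within- and between-group differences in PGSI and MTM constructs over time (pre-, post-, follow-up), to assess efficacy of the MTM-based intervention".

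Section 2.4 places the pre-test in the Week 1 session, which consists of "orientation, completion of the pre-intervention survey, and the start of the intervention activities". The pre-test is therefore an outcome wave measured before treatment begins.

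Adjustment for baseline by ANCOVA is planned in Section 2.13 only when a baseline difference is found to be significant. Section 2.3 gives the power inputs without saying which effect of the ANOVA they refer to. The article nowhere names the group-by-time interaction, or a between-arm contrast of change, as the test of efficacy.

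**The concern.** In a mixed ANOVA with a pre-test wave, three terms come out.

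- **Group** compares the arms on the average of all three waves. Randomisation makes the expected pre-test difference zero, so this average is pulled toward zero, and it carries along any chance difference at pre-test.
- **Time** describes change pooled over both arms. It does not compare them.
- **Group-by-time** asks whether change differs between arms. It is the term in this model that isolates an intervention effect.

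The aim in Section 1 is comparative: the MTM-based arm against a knowledge-based arm. Section 2.13 nevertheless ties the intervention to the first term, and Table 3 adds within-group differences as evidence of efficacy. An analyst who follows this literally could miss a real benefit and would report a shrunken one. A fall in PGSI in both arms could also be presented as support for the MTM programme. Such a fall is plausible without any MTM-specific effect, because entry requires a PGSI of 3 or more and both arms attend sessions.

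**Working it through.** **Inputs from the protocol.** Section 2.3 uses an effect size of 0.30 with two arms and three waves, at 80% power and a 0.05 significance level. For the repeated measures it "assumed a correlation of 0.5 among repeated measures and applied a non-sphericity correction of 1". It reports 20 per group required, raised to 30 per group.

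**Assumptions not in the protocol.** The 0.30 is Cohen's f. For the power comparison, outcomes have unit SD with equal correlation ρ = 0.5 between waves, tests are two-sided at 0.05, and the true benefit d is 0.5 SD.

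**Step 1. The plan's own figure.** The usual repeated-measures formulas with f = 0.30, m = 3 waves and total N are:

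- Group-by-time: λ = f²·N·m/(1−ρ), df 2 and 2(N−2). At N = 20, λ = 0.09·20·3/0.5 = 10.8 and power is 81.2%. At N = 40, power is 98.8%.
- Between-group: λ = f²·N·m/(1+2ρ), df 1 and N−2. At N = 40, λ = 0.09·40·3/2 = 5.4 and power is 62.0%. At N = 60 it is 79.9%; 80% needs N = 62.

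Twenty per group is not reproduced for either term. Twenty in total fits group-by-time, and equally the pooled time effect. That discrepancy is a separate matter. Here it shows only that Section 2.3 does not settle which term was meant.

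**Step 2. What the group effect estimates.** If the arm differences at pre-test, post-test and follow-up are (0, d, d), their mean is 2d/3. If they are (0, 0, d), it is d/3. With d = 0.5 these are 0.33 and 0.17 SD.

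**Step 3. Power, n per arm.**

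- Group effect: SE = √[(2/n)(1+2ρ)/3]. At n = 20, SE = 0.258 and 0.333/0.258 = 1.29. At n = 30, SE = 0.211 and the ratio is 1.58.
- Group-by-time: the differences deviate from their mean by (−2d/3, d/3, d/3), with sum of squares 2d²/3. So λ = (n/2)(2d²/3)/(1−ρ), which is 3.33 at n = 20 and 5.00 at n = 30. The pattern (0, 0, d) has the same sum of squares.
- Eight-week contrast adjusted for pre-test: SE = √[(2/n)(1−ρ²)]. At n = 20, SE = 0.274 and 0.5/0.274 = 1.83. At n = 30, SE = 0.224 and the ratio is 2.24.

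| Term (d = 0.5) | 20 per arm | 30 per arm |
|---|---|---|
| Group effect, benefit at both later waves | 24% | 34% |
| Group effect, benefit at follow-up only | 10% | 12% |
| Group-by-time, either pattern | 34% | 49% |
| Baseline-adjusted eight-week contrast, either pattern | 43% | 59% |

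With a larger assumed benefit of 0.8 SD at both later waves, the group effect has 52% and group-by-time 73% at 20 per arm (70% and 90% at 30).

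**Step 4. Chance imbalance.** With no treatment effect, a 0.3 SD pre-test gap is expected to shrink to ρ·0.3 = 0.15 SD at each later wave. The group estimate then shifts by (0.3+0.15+0.15)/3 = 0.20 SD. At 30 per arm such a gap has z = 0.3/√(2/30) = 1.16. A gap of at least this size occurs about 25% of the time in either direction, or about 12% in the direction favouring the intervention. At z = 1.16 the gap is not significant, so the conditional ANCOVA would not be triggered.

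**The case against.** The best defence is that Section 2.13 is loosely worded rather than mistaken. The phrase main effect never appears. Both glosses are introduced as examples, so they do not formally designate a test. Differences between groups over time, as in Table 3, is a common lay way of saying group-by-time, and the software prints that term by default. The non-sphericity input in Section 2.3 has no role in a one-degree-of-freedom between-subject test, which suggests that the power calculation concerned a term involving time. The article is also condensed, and the choice of contrast is often left to an analysis plan.

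Most of this stands, and it limits the point. A reader might infer that the protocol has adopted the two main effects as its efficacy tests; the text does not go that far. What remains is that the only effect described as being due to the intervention is the between-group one. That is a wrong attribution, not an omitted detail.

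A reader might also infer that the group effect produces excess false positives. It does not: averaged over randomisation, its type I error is 5%. Even given a pre-test gap of exactly 0.3 SD that regresses as in Step 4, rejection under no effect was simulated at about 4% at 30 per arm and 2% at 20. Larger gaps do raise it. The harm from imbalance is a shifted estimate in the particular trial.

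Finally, a baseline-adjusted mean of post-test and follow-up reaches 59% and 77% power under the two-wave pattern. Those figures should not be credited to the eight-week contrast, because they belong to a different estimand.

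**Conclusion.** The point holds as a should-fix on wording. Taken literally, Section 2.13 and Table 3 read efficacy from a term that estimates 2/3 of the true difference, or 1/3 if the benefit appears late. At d = 0.5 that term gives up 10 to 15 percentage points of power against group-by-time (24% against 34%, and 34% against 49%) and 19 to 25 points against a baseline-adjusted eight-week contrast. Its estimate moves with chance pre-test imbalance that the conditional ANCOVA would often leave alone, and within-arm change could be presented as efficacy although it compares nothing.

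The 2/3 and 1/3 factors follow from the design and the assumed timing of benefit alone. The power figures rest on the assumed 0.5 SD and compound symmetry, with only ρ = 0.5 taken from the protocol. The documents do not show that the investigators intend to ignore group-by-time, nor that the error rate is inflated.

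**What to change.** In Section 2.13 and Table 3:

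1. State that efficacy rests on the between-arm difference in change (group-by-time) or, better, on a between-arm PGSI contrast with pre-test PGSI always in the model, in place of adjustment only after a significant baseline test.
2. Name the time point before analysis: eight weeks, or the mean of post-test and follow-up. This is the investigators' choice. The mean is more powerful if benefit is present at both waves; the eight-week contrast keeps its power if benefit comes late.
3. State that the overall group effect and within-arm changes are descriptive and do not support an efficacy claim.
4. Remove or reword the gloss that ties the between-group effect to the intervention.

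The cost is a few sentences. Data, visits, sample and software are unchanged. It should be done before outcome data are analysed, so that the term called efficacy is not chosen with the results in view.

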### 2.10. Data Analysis

The primary objective of this study is to evaluate the efficacy of an MTM-based intervention [10] in promoting responsible gambling behaviors among college students. The intervention is designed to help participants recognize the advantages of responsible gambling while addressing common barriers, enhance participatory dialogue, build behavioral confidence, and facilitate changes in their physical and social environments. Additionally, the intervention aims to foster emotional transformation and implement strategies for maintaining responsible gambling behavior over time. Data analysis will be conducted using SAS 9.4 (SAS Institute Inc., Cary, NC, USA), with a significance level of 0.05 for all statistical analyses to determine the effectiveness of the intervention. This will allow for a comprehensive evaluation of how the MTM-based approach impacts gambling behaviors and the sustainability of responsible gambling habits in the target population.

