This study relies on the PGSI as one of the key outcome measures. While the PGSI is a widely validated and commonly used instrument, its 12-month recall period may limit its sensitivity to detecting short-term behavioral changes resulting from the intervention. To address this, we will supplement our analyses with MTM construct scores, which are specifically designed to measure short-term behavioral initiation and sustenance. Additionally, we will conduct item-level analyses of the PGSI responses (e.g., related to gambling expenditure, time lost, or emotional impact) to assess whether certain dimensions demonstrate greater sensitivity to short-term change. While the PGSI was selected for its classification utility and comparability across studies, we acknowledge that it is best suited for long-term assessments. Accordingly, we are also exploring the feasibility of a 6- to 12-month follow-up study to better align with the PGSI’s recall window and to assess sustained changes in gambling behavior. This extension will depend on participant retention and funding availability but would provide a more complete evaluation of the intervention’s longitudinal impact.

While simple randomization is used for group assignment, we acknowledge that this method may result in imbalances in baseline characteristics, particularly in smaller samples. Although reproducibility was ensured through the use of a fixed seed in SAS, future studies may benefit from using stratified or block randomization to enhance group comparability.

Lastly, the self-reported nature of gambling behaviors, while necessary for understanding personal habits and attitudes, introduces the potential for recall and social-desirability biases. The participants may underreport or overreport their gambling behaviors due to memory lapses or the desire to present themselves in a more socially acceptable light. To address these biases, future studies could incorporate objective measures or third-party reports to provide a more accurate assessment of gambling behaviors and the intervention’s impact.

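### Baseline adjustment depends on a significant baseline test, so the usual efficacy analysis forgoes precision and its estimate shifts with chance imbalance

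*Protocol article*

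**What the plan says.** Section 2.12 of the protocol article plans chi-square and independent t-tests between arms at pre-test. Of the t-test it says: "It will be employed at the pre-test to evaluate differences in MTM constructs and other continuous variables between the experimental and comparison groups". Table 3 gives that test the purpose "Assess baseline equivalence in continuous variables (e.g., PGSI, MTM scores) across groups", and gives the chi-square test the same purpose for categorical variables. No equivalence margin is stated. Section 2.10 sets alpha "with a significance level of 0.05 for all statistical analyses", which covers these tests too.

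Section 2.13 makes a two-way mixed ANOVA over pre-test, post-test and follow-up the efficacy analysis for PGSI and MTM scores. ANCOVA is added only "If significant baseline differences are identified in key variables", with PGSI, MTM scores, age and gender as examples. Table 3 repeats the condition: "Adjust for baseline differences in key variables (e.g., age, PGSI) when detected". Section 2.13 also credits ANCOVA with better precision. Section 3.2 concedes that, with simple randomisation, "this method may result in imbalances in baseline characteristics, particularly in smaller samples".

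**The concern.** A baseline p-value is a poor switch for choosing the efficacy model, for two reasons.

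- **It measures the wrong thing.** If randomisation is sound, the baseline null hypothesis is true and the test is significant at its nominal rate. The effect of a chance gap on the result depends on the size of the gap and on the correlation between pre-test and later scores, not on whether p falls below 0.05. A non-significant result in a sample this small is also no evidence of equivalence.
- **ANCOVA helps without any imbalance.** Adjusting for the pre-test score reduces residual variance in every trial. The rule withholds this gain unless a test happens to be significant.

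At stake are power in a 60-person trial and an effect estimate that moves with the direction of whatever imbalance arose. If the experimental arm starts with higher PGSI scores, regression to the mean looks like benefit. If it starts lower, benefit is partly hidden.

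**Working it through.** **Inputs from the protocol article.** Alpha is 0.05 (Section 2.10; two-sided assumed). Section 2.3 gives the design as "with a medium effect size of 0.30, two intervention groups, three time points (pre-, post-, and follow-up") and states that "the analysis assumed a correlation of 0.5 among repeated measures and applied a non-sphericity correction of 1". It gives 20 per group, raised by 50%: 20 × 1.5 = 30 per arm.

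**The plan's own figure.** No figure is given for the baseline tests or the ANCOVA rule. The stated sample-size inputs, applied to the group-by-time test, give noncentrality 0.30² × 20 × 3 / (1 − 0.5) = 10.8 and power 0.812 at 20 participants in total, so 20 per group is not reproduced. That is a separate matter. Only the 30 randomised per arm is used below, with 20 per arm as the completer case.

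**Assumed here, not in the documents.** A true effect of 0.5 SD at both later visits (0.6 also shown), equal correlation ρ between visits, and normal scores.

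**Step 1: when the trigger fires.** The smallest significant observed gap is t(0.975, 2n − 2) × √(2/n):
- n = 30: 2.002 × 0.258 = 0.52 SD
- n = 20: 2.024 × 0.316 = 0.64 SD

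An observed gap of 0.5 SD at 30 per arm gives t = 0.5/0.258 = 1.94, p = 0.058. An outcome's own test is significant in 5% of trials. If any of 7 to 12 independent tests can trigger adjustment, at least one fires in 1 − 0.95⁷ = 30% to 1 − 0.95¹² = 46% of trials, though possibly for another variable.

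**Step 2: precision of the same contrast, with and without adjustment.** Take the mean of post-test and follow-up. Per-person variance, in SD² units:
- minus pre-test (change score): 1.5(1 − ρ)
- adjusted for pre-test (ANCOVA): (1 + ρ)/2 − ρ²

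At ρ = 0.5 these are 0.75 and 0.50, a third less. At 30 per arm, SE = √(0.75 × 2/30) = 0.224 and √(0.50 × 2/30) = 0.183 (0.184 in simulation). At ρ = 0.7 they are 0.45 and 0.36 (20% less). At ρ = 0.9 they are 0.15 and 0.14 (7% less).

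**Step 3: power (simulation, 3,000 trials per row).** The rule column uses ANCOVA if the outcome's own baseline p < 0.05, and otherwise the group-by-time test.

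| ρ | n per arm | Effect (SD) | Group-by-time, 2 df | Change, 1 df | Conditional rule | ANCOVA always, 1 df |
|---|---|---|---|---|---|---|
| 0.3 | 30 | 0.5 | 38% | 47% | 40% | 72% |
| 0.5 | 30 | 0.5 | 49% | 59–60% | 51% | 76% |
| 0.7 | 30 | 0.5 | 72% | 81% | 73% | 88% |
| 0.5 | 20 | 0.5 | 34% | 43% | 35% | 57% |
| 0.5 | 30 | 0.6 | 65% | 74% | 67% | 88% |

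At ρ = 0.5 the 2-df test and the 1-df change score have the same noncentrality, (0.5/0.224)² = 5. The step from 49% to 59% therefore comes from the choice of contrast, and the step from 59% to 76% comes from adjustment.

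**Step 4: effect of an unflagged gap.** The expected shift in the change estimate is (1 − ρ) × gap. About 20% of sound randomisations at 30 per arm (30% at 20 per arm) leave a non-significant gap above 0.3 SD. At 30 per arm such gaps lie between 0.30 and 0.52 SD and average about 0.39 SD, so the shift at ρ = 0.5 is 0.5 × 0.39 ≈ 0.19 SD. The simulated change estimate averages about 0.69 or 0.30 SD, depending on direction, against a true 0.50. ANCOVA stays at 0.50 either way.

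**Step 5: false positives.** With no effect (ρ = 0.5, 30 per arm), the group-by-time test rejects in about 5% of all trials. In trials with an unflagged gap above 0.3 SD it rejects in 6.5% to 7.7%, depending on the run.

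**The case against.** The strongest reply is that the mixed ANOVA already handles baseline. The pre-test is one of its three levels, so the group-by-time test compares changes and subtracts an additive gap in every trial. It is also valid over randomisation (step 5). This stands. A reader might infer that unflagged imbalance is ignored, that the trigger is the only protection, or that false positives are inflated; the model does not support those readings. What remains is regression to the mean and lost precision. Section 2.13 also mentions between-group effects. A group main effect averaged over all three visits would be more exposed, because it includes the baseline gap.

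Other stronger readings also fail:

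- **The t-test misses a 0.5-SD imbalance about half the time.** The arithmetic is right (power 0.478 at 30 per arm), but it assumes a true population difference, which randomisation rules out. The relevant figure is the 0.52-SD threshold for the observed gap.
- **Adjustment is withheld in 95% of trials.** This holds only for an outcome's own baseline test. With several possible triggers, some adjustment is more frequent (step 1).
- **The plan concludes equivalence.** Table 3 says the tests assess it, and no sentence accepts the null hypothesis. The label is still wrong for these tests.
- **The model is chosen after seeing outcomes.** The rule is prespecified and uses baseline data only.

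The gain also depends on correlation. PGSI has a 12-month recall period (Sections 2.9 and 3.2), so its recall windows overlap heavily across this study and its correlation may exceed 0.5. The documents give no other value. At 0.9 almost nothing would be gained.

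**Conclusion.** The point holds as one of efficiency and of sensitivity to the imbalance that happens to arise, not of invalid inference. At 30 per arm, correlation 0.5 and an assumed 0.5-SD effect at both later visits, unconditional adjustment cuts the variance of the same contrast by a third and raises its power by about 17 points (59% to 76%). At correlation 0.7 the gain is about 7 points (81% to 88%). The larger distance from the planned 2-df test (49%) to ANCOVA (76%) should not be credited to adjustment alone: about 10 points come from averaging the two later visits, which pays off because the effect is assumed equal at both. In roughly one trial in five, an unflagged gap would shift the change estimate by about 0.2 SD in either direction, while ANCOVA would not shift.

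**What to change.** - **Section 2.13:** delete the significance trigger. Prespecify that every PGSI and MTM efficacy comparison models post-test and follow-up as outcomes, with group, time, group-by-time and that outcome's own pre-test value as terms, whatever the baseline data show. The pre-test is then a covariate and not also an outcome level. State that efficacy is read from the group effect averaged over the two later visits. In this model, group-by-time only asks whether the effect differs between them.
- **Table 3:** remove the conditional wording from the ANCOVA row and the equivalence purpose from the chi-square and t-test rows.
- **Section 2.12:** report baseline characteristics by arm descriptively (means, SDs, standardised differences, counts and percentages), without significance tests as evidence of equivalence.

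The cost is wording in three places and one degree of freedom per model. No extra data or participants are needed.
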